### 7.2 Randomisation, blinding and treatment allocation

The study is a single blinded randomized cross-over trial. The code will be broken only after all patients have completed the protocol. However, in case of any serious adverse event, if necessary, the individual code for the concerning participant will be broken, to enable and facilitate possible medical treatment.

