## SUMMARY

**Rationale:** In acute myocardial infarction early restoration of coronary blood flow is the most effective strategy to limit infarct-size. Paradoxically, reperfusion itself also aggravates myocardial injury and contributes to final infarct size, a process termed 'reperfusion injury'. Ischemia and reperfusion (IR)-induced endothelial dysfunction seems to play a pivotal role in this process, resulting in vasoconstriction and reduced blood flow to the already ischemic tissue. Recently, it has been shown that the glucose-lowering drug metformin is able to limit IR-injury in murine models of myocardial infarction, probably by increased formation of the endogenous nucleoside adenosine. In the current research proposal, we aim to translate this finding to the human in vivo situation, using flow-mediated dilation (FMD) of the brachial artery as a well-validated model of (endothelial) IR-injury.

**Objective:** To study the protective effect of pre-treatment with metformin on flow mediated dilation after 20 minutes ischemia and 20 minutes reperfusion. If metformin treatment indeed limits endothelial IR-injury, a second, unblinded study will be performed in the same subjects to investigate whether this is mediated by adenosine receptor stimulation.

**Study design:** Randomized, single blind, , cross over clinical trial.

**Study population:** Healthy volunteers (n= 26 for both studies), age 30-50 years.

**Intervention:** *Main study (metformin FMD trial):* Pre-treatment with metformin 500 mg three times a day for 3 days or no medication. *Second study:* Pre-treatment with metformin 500 mg three times a day for 3 days or no medication, combined with caffeine infusion preceding FMD measurement.

**Main study parameters/endpoints:** Difference in flow mediated dilation before and after 20 minutes of ischemia.

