### 3. STUDY DESIGN

After written informed consent all healthy volunteers will undergo medical screening consisting of a short interview, physical examination, laboratory evaluation (glucose, cholesterol, kreatinine) and EKG. Females using oral contraceptives will be asked to continue their contraceptive throughout the study to maintain stable hormone levels. Females not on oral contraceptives will be measured at identical times in their menstrual cycle. As this is a cross-over model and subjects are their own control, potential differences in baseline FMD are not to be expected to influence results. For both trials, volunteers eligible for trial participation will receive study medication and instructions how to use it. The first study is a randomized, single-blinded cross-over study. 26 participants will be recruited and half of the participants will be pretreated with metformin 500 mg three times a day for 3 days, to ensure a steady state plasma concentration, whereas the other half will receive no medication. The two experiments will be separated by approximately two weeks to prevent any cross-over effect of metformin. The last dose of metformin will be given approximately 3 hours before the experiments. The FMD measurements will be performed, by an operator blinded for pretreatment after an overnight fast and 24 hours of caffeine abstinence (since caffeine is an adenosine receptor antagonist). Also, the participants have to refrain from strenuous exercise for at least 24 hours before the experiment, as this potentially act as a preconditioning stimulus. Experiments will be performed in a temperature-controlled room (22° C) and according to recent guidelines for assessment of the FMD. Measurements will always be performed at the same time of day to prevent diurnal variation in the FMD response.

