When metformin displays a protective effect on endothelial function in this RCT, a second experiment will be conducted in the same volunteers to further elucidate the underlying mechanism. For this experiment the design will be identical to the metformin-FMD trial, with the exception that the subjects will all be pretreated with caffeine (4 mg/kg intravenously over 10 minutes) prior to the FMD measurement. This dose has previously been shown to completely prevent the protective effect of ischemic preconditioning which is also mediated by adenosine receptor stimulation in another human experimental model of forearm ischemia-reperfusion injury. This study will provide the answer to the question whether the protective effect of metformin is mediated by adenosine receptor stimulation by comparing the results of the FMD measurements with and without concomitant administration of caffeine. In addition, this study will enable us to exclude that any effect of caffeine on metformin-induced protection is due to a direct effect of caffeine on FMD or on the effect of IR on FMD: this will be studied by comparing the FMD measurements after caffeine administration in the placebo-arms.

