### **9.4 Interim analysis (if applicable)**

Not applicable

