#### **10.6 Incentives (if applicable)**

Volunteers will be paid 300 euro at completion of the protocol (i.e. four experiments) as a compensation. Should the volunteer decide to withdraw from the study before the last measurement, then the compensation will be proportional to the number of experiments that the subject has participated in (e.g. if the subjects withdraws after the first RCT, than 150 euro's will be paid).

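### The code-break rule in 7.2 leaves no point at which the study 1 result that decides on study 2 can be known, and the protocol disagrees with itself on whether study 2 is blinded

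*Protocol*

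**What the plan says.** Study 2 is conditional on the result of study 1. Section 3 states: "When metformin displays a protective effect on endothelial function in this RCT, a second experiment will be conducted in the same volunteers". The Summary sets the same condition: "If metformin treatment indeed limits endothelial IR-injury, a second, unblinded study will be performed in the same subjects". The Introduction also makes the second experiment depend on metformin having been proven effective.

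Section 7.2 controls when allocation becomes known: "The code will be broken only after all patients have completed the protocol". Its one exception is that "in case of any serious adverse event, if necessary, the individual code for the concerning participant will be broken". Section 10.6 shows what completing the protocol means: "Volunteers will be paid 300 euro at completion of the protocol (i.e. four experiments) as a compensation".

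On masking, Section 3 says of study 1: "The FMD measurements will be performed, by an operator blinded for pretreatment". It then says that study 2 has the same design apart from caffeine for all subjects. Section 7.2 describes the study as single blinded and does not separate its two parts.

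Section 9.2 names a paired t-test as the test of metformin's effect. Section 9.4 marks interim analysis as not applicable.

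**The concern.** The decision to start study 2 needs a comparison of metformin with no medication within each volunteer. That comparison cannot be made without knowing which visit followed metformin. If the code stays closed until all four experiments are done, the information needed to start study 2 arrives after study 2 has finished.

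The blinding of study 2 matters in its own right. FMD is an ultrasound measurement in which the operator obtains and optimises the image, and the operator's blinding is the only masking that Section 3 describes. Section 3 answers the mechanistic question by comparing FMD results with and without caffeine, that is, across the two studies. If the operator is masked in study 1 and not in study 2, that comparison mixes the effect of caffeine with a change in measurement conditions.

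**Working it through.** **1. What completing the protocol covers.** Section 10.6 pays 300 euro for four experiments, which is 300 / 4 = 75 euro each. It pays 150 euro to a volunteer who leaves after the first RCT, and 150 / 75 = 2 experiments. So study 1 is two experiments, and the full protocol is study 1 plus study 2.

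**2. What the decision needs.** The test in 9.2 pairs each volunteer's metformin visit with the no-medication visit. It needs the allocation by period for all volunteers. The serious adverse event exception in 7.2 releases single codes for medical care and does not provide this.

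**3. The two possible readings of 7.2.**

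- *7.2 covers both studies.* This follows from its wording taken with 10.6. The study 1 allocation opens only after study 2, so the condition in the Summary and Section 3 cannot be evaluated in time. The code also stays closed during study 2, which contradicts the Summary's description of study 2 as unblinded.
- *7.2 covers study 1 only.* The code opens after the second experiment of study 1, and the condition can be evaluated. But 7.2 does not limit itself in this way, and no code rule is then written for study 2. The Summary (unblinded) and Section 3 (same design as a trial with a blinded operator) still disagree.

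At least one statement fails under either reading.

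**4. Whether the sample size is affected.** Inputs from section 4.4: SD 3.7, assumed correlation 0.7, difference 1.65, type I error 5%, power 80%, n = 26.

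- SD of the paired difference = 3.7 × √(2 × (1 − 0.7)) = 2.87 (stated: 2.85).
- Noncentrality = 1.65 / 2.85 × √26 = 2.95, with 25 degrees of freedom.
- Power of the two-sided 5% paired t-test = 81.0% with SD 2.85, or 80.5% with SD 2.87. The smallest n that reaches 80% is 26.
- A one-sided 5% test would have 89% power. The stated 80% therefore fits a two-sided test, although the protocol does not give the sidedness.

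The stated n reproduces and does not depend on when the code is opened.

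**The case against.** The strongest reply is that the Summary calls study 2 unblinded, so the single-blind rule and its code belong naturally to study 1. Section 3 describes the first study in almost the same terms as 7.2, and the four-experiment gloss comes from the payment section, not from the code-break rule. Section 10.6 itself treats the first RCT as a separable unit. On this view the code opens after study 1 and the decision can be made. This is a fair reading, and it shows that the conflict can be resolved. It is not what 7.2 says, though, and it leaves the blinding of study 2 contradictory.

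A reader might also infer more than the documents support:

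- *That section 9.4 is contradicted too.* One analysis after all subjects have finished study 1 is that study's final analysis, not an interim look, so 9.4 is consistent.
- *That any favourable trend could launch study 2.* The Introduction requires proven effectiveness, 9.2 names the test and 4.4 sets a 5% error rate. Together these point to the planned test, although no sentence says so. An explicit rule could also stand in an analysis plan that is not shown.
- *That the measuring team will unblind itself.* Nothing in the text says this. Section 8.2.1 has the on-call pharmacist break a code when a serious event requires it. What can be said is that no separation of roles is written for the study 1 analysis.

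**Conclusion.** The point holds as an internal inconsistency that should be fixed. The Summary and Section 3 require the study 1 result before study 2. Section 7.2, with the gloss in 10.6, withholds the allocation until after study 2, and no exception covers the study 1 analysis. Separately, the Summary and Section 3 disagree on whether study 2 is blinded. The code-break and blinding rules cannot all be followed as written.

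The defect has no numerical size. It concerns the sequence of steps and the masking of a conditional mechanistic study. The study 1 primary comparison, its test and n = 26 stand. It would go too far to say that the decision is impossible under every reading, because a restriction of 7.2 to study 1 would allow it. The conclusion rests on taking completion of the protocol in 7.2 in the sense that 10.6 gives it, the only place where the protocol spells it out.

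**What to change.** - **Section 7.2, study 1 code.** State that it is broken once all subjects have completed both study 1 experiments and the FMD readings are locked. Someone not involved in scanning or reading breaks it and runs the paired t-test of 9.2 once, as the final study 1 analysis.
- **Criterion.** State that study 2 starts only if that test favours metformin at the planned 5% level. Give the sidedness; two-sided is assumed here because it fits the stated power.
- **Study 2 blinding.** Reconcile the Summary, Section 3 and 7.2 so that the operator and reader stay blinded to pretreatment in study 2, with a separate code kept closed until the study 2 readings are locked.
- **Section 9.4** can stay as it is.

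The cost is a few sentences and a small separation of roles within the team, with no extra subjects or visits. One limit remains: the decision to proceed tells the operator that study 1 was positive. Any conditional design does this. It does not reveal which study 2 visit followed metformin, and that is the blinding that guards against biased measurement.

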### 7.3 Study procedures

#### Enrollment check:

At entry of this study all volunteers will undergo an enrolment check consisting of a medical interview and physical examination performed by a qualified physician. EKG and venous puncture will be performed for some screening lab tests (total cholesterol, renal function (creatinine) and glucose). Just before the FMD measurement, a venous puncture will be performed for the determination of caffeine and metformin concentration.

#### Medication:

In both studies, all volunteers are treated with either metformin (500 mg tid for 3 days) until the day of experiment.

In the second part of the study all subjects will receive caffeine (4 mg/kg intravenously infused over 10 minutes) immediately before the first FMD measurement.

#### FMD measurement:

As described in section 3, study design.

## **7.4 Withdrawal of individual subjects**

Subjects can leave the study at any time for any reason if they wish to do so without any consequences. The investigator can decide to withdraw a subject from the study for urgent medical reasons.

### **7.4.1 Specific criteria for withdrawal (if applicable)**

Not applicable

## **7.5 Replacement of individual subjects after withdrawal**

If a participant decides to withdraw from the trial, replacement will be recruited in the same fashion the original participants were recruited.

## **7.6 Follow-up of subjects withdrawn from treatment**

A participant who decides to withdraw from the trial will be invited to an exit-interview concerning their withdrawal.

## **7.7 Premature termination of the study**

In case there of any unexpected and unforeseen complication or side-effect that is related to our study, continuation of the protocol will be discussed with responsible investigators and local ethics committee.

## 8. SAFETY REPORTING

### 8.1 Section 10 WMO event

In accordance to section 10, subsection 1, of the WMO, the investigator will inform the patients and the reviewing accredited METC if anything occurs, on the basis of which it appears that the disadvantages of participation may be significantly greater than was foreseen in the research proposal. The study will be suspended pending further review by the accredited METC, except insofar as suspension would jeopardise the patients' health. The investigator will take care that all patients are kept informed.

### 8.2 Adverse and serious adverse events

Adverse events are defined as any undesirable experience occurring to a subject during the study, whether or not considered related to the investigational drug. All adverse events reported spontaneously by the subject or observed by the investigator or his staff will be recorded.

A serious adverse event is any untoward medical occurrence or effect that at any dose:

- results in death;
- is life threatening (at the time of the event);
- requires hospitalisation or prolongation of existing inpatients' hospitalisation;
- results in persistent or significant disability or incapacity;
- is a congenital anomaly or birth defect;
- is a new event of the trial likely to affect the safety of the subjects, such as an unexpected outcome of an adverse reaction, lack of efficacy of an IMP used for the treatment of a life threatening disease, major safety finding from a newly completed animal study, etc.

All serious adverse events will be reported to the sponsor of this trial: Prof. [name], head of the department of Pharmacology and Toxicology. He delegates the appropriate handling of these events to the coordinating and principle investigators of this trial: Prof. dr. [name] and Dr. [name], Further report of these adverse events will be performed according to GCP as outlined below.

All SAEs will be reported through the web portal *ToetsingOnline* to the accredited METC that approved the protocol, within 15 calendar days after the sponsor has first knowledge of the serious adverse reactions.

SAEs that result in death or are life threatening should be reported expedited. The expedited reporting will occur not later than 7 calendar days after the responsible investigator has first knowledge of the adverse reaction. This is for a preliminary report with another 8 days for completion of the report.

### **8.2.1 Suspected unexpected serious adverse reactions (SUSAR)**

Adverse reactions are all untoward and unintended responses to an investigational product related to any dose administered.

Unexpected adverse reactions are adverse reactions, of which the nature, or severity, is not consistent with the applicable product information (e.g. Investigator's Brochure for an unapproved IMP or Summary of Product Characteristics (SPC) for an authorised medicinal product).

The sponsor will report expedited the following SUSARs through the web portal *ToetsingOnline* to the METC:

- SUSARs that have arisen in the clinical trial that was assessed by the METC;
- SUSARs that have arisen in other clinical trials of the same sponsor and with the same medicinal product, and that could have consequences for the safety of the subjects involved in the clinical trial that was assessed by the METC.

The remaining SUSARs are recorded in an overview list (line-listing) that will be submitted once every half year to the METC. This line-listing provides an overview of all SUSARs from the study medicine, accompanied by a brief report highlighting the main points of concern. The expedited reporting of SUSARs through the web portal *ToetsingOnline* is sufficient as notification to the competent authority.

The sponsor will report expedited all SUSARs to the competent authority, through the portal of the CCMO, who will subsequently report to the Medicine Evaluation Board and the competent authorities in other Member States. If a SAE or SUSAR occurs and there is the need to know whether a patient was treated with metformin or placebo, the pharmacist on call can be contacted (24 hours a day, 7 days a week) and he/she will be able to break the blinding code for that particular participant. The expedited reporting will occur not later than 15 calendar days after the sponsor has first knowledge of the adverse reactions. For fatal or life threatening cases the term will be maximal 7 days for a preliminary report with another 8 days for completion of the report.

### **8.2.2 Annual safety report**

In addition to the expedited reporting of SUSARs, the sponsor will submit, once a year throughout the clinical trial, a safety report to the accredited METC, competent authority, Medicine Evaluation Board and competent authorities of the concerned Member States.

This safety report consists of:

- a list of all suspected (unexpected or expected) serious adverse reactions, along with an aggregated summary table of all reported serious adverse reactions, ordered by organ system, per study;
- a report concerning the safety of the subjects, consisting of a complete safety analysis and an evaluation of the balance between the efficacy and the harmfulness of the medicine under investigation.

### **8.3 Follow-up of adverse events**

All adverse events will be followed until they have abated, or until a stable situation has been reached. Depending on the event, follow up may require additional tests or medical procedures as indicated, and/or referral to the general physician or a medical specialist.

### **8.4 Data Safety Monitoring Board (DSMB)**

Not applicable.

## **9. STATISTICAL ANALYSIS**

### **9.1 Descriptive statistics**

Descriptive statistics will be presented as mean  $\pm$ SD, unless otherwise specified.

### **9.2 Univariate analysis**

A paired-sample t-test will be used to test whether metformin can attenuate the decrease in FMD after forearm IR. The same method will be used in the second study to explore the effect of caffeine on metformin-induced protection, and the effect of caffeine on FMD per se.

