##### 4.4 Sample size calculation

A recent study with a similar experimental design from our research group has reported that the FMD averages 7.7% before, and 5.1% after forearm IR. Therefore, the effect of IR

on FMD is 2.6% with a SD of 3.7%. However, this study did not have a cross-over design. A previous cross-over study from [name] et al. (unpublished results) has reported a Spearman correlation coefficient of 0.53 between the two paired FMD measurements, but in this study one of the FMD measurements was preceded by ischemic preconditioning. Thus, the correlation coefficient with two similar measurements of FMD is most likely stronger than 0.53. Assuming a correlation coefficient of 0.7, the expected SD of the effect of IR on FMD in our study therefore equals 2.85. With  $n = 26$  subjects, we will be able to detect a difference of 1.65% with a power of 80% and a type I error probability of 5%, which is a relevant difference.

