## 7. METHODS

### 7.1 Study parameters/endpoints

#### 7.1.1 Main study parameter/endpoint

Difference in flow mediated dilation before and after 20 minutes of forearm ischemia and reperfusion.

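### The primary paired t-test leaves period out of a randomised two-sequence cross-over, so a period effect would cost power, and would bias the estimate if replacements leave the sequences unequal

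*Protocol*

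**What the plan says.** Protocol section 3 sets the design: "The first study is a randomized, single-blinded cross-over study". On order of treatment it says "26 participants will be recruited and half of the participants will be pretreated with metformin 500 mg three times a day for 3 days", with the other half untreated first. On spacing: "The two experiments will be separated by approximately two weeks to prevent any cross-over effect of metformin". This is a two-sequence, two-period cross-over, planned as 13:13.

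Section 7.1.1 defines the endpoint as "Difference in flow mediated dilation before and after 20 minutes of forearm ischemia and reperfusion", which is a change measured within one session.

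Section 9.2 gives the test: "A paired-sample t-test will be used to test whether metformin can attenuate the decrease in FMD after forearm IR". Section 9.3 marks multivariate analysis as not applicable. Neither period nor sequence is mentioned in any section.

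On withdrawals, section 7.5 says "If a participant decides to withdraw from the trial, replacement will be recruited in the same fashion the original participants were recruited". It does not say which sequence the replacement receives.

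**The concern.** A paired t-test on the metformin-minus-control differences pools the two sequences as if order did not exist. If the IR-induced change differs between first and second visit, for example because the first 20-minute ischemia is experienced differently from the second, the differences shift up in one sequence and down in the other. With equal sequences the shifts cancel in the mean but remain in the variance, so the test loses power that the design could have kept. With unequal sequences they no longer cancel, and part of the period effect is read as a metformin effect.

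The power of this test also matters beyond the first study, because section 3 makes the second study depend on a protective effect being seen in the first.

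**Working it through.** **Inputs.** From Protocol section 4.4: "on FMD is 2.6% with a SD of 3.7" percentage points; "Assuming a correlation coefficient of 0.7, the expected SD of the effect of IR on FMD in our study therefore equals 2.85"; n = 26; detectable difference 1.65; power 80%; type I error 5% (sidedness not stated, two-sided taken). Assumed: P, the difference between periods in the IR-induced change, from 0 to 2 points; and, for the unequal case, a 15:11 split.

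**1. The plan's own figure.** SD of the paired difference = 3.7 × √(2 × (1 − 0.7)) = 2.87, against 2.85 stated. Noncentral t, 25 df, SD 2.85: power at 1.65 is 81.0%, and the difference detectable with 80% power is 1.63. The stated figure reproduces and is not in dispute.

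**2. How P enters.** Let τ be the metformin effect and P the second-period minus first-period difference. The metformin-minus-control difference has mean τ − P when metformin comes first and τ + P when it comes second, with SD 2.85 around each.

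- Mean over all 26: τ + P × (n₂ − n₁)/26, where n₁ and n₂ count the metformin-first and metformin-second subjects. At 13:13 this is τ, whatever P is.
- Expected sample variance at 13:13: 2.85² + P² × 26/25. At P = 1 the SD used by the test is about √(8.12 + 1.04) = 3.03; at P = 2 it is about √(8.12 + 4.16) = 3.50.

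The mean difference itself varies no more than before; only its estimated standard error grows. Putting the larger SD straight into a power formula would therefore overstate the loss, so power was simulated with P as a fixed shift.

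**3. Power and type I error at 13:13** (effect 1.65, 100,000 to 200,000 runs per setting):

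| P (points) | Paired t, power | Paired t, type I error | Period-adjusted, power |
|---|---|---|---|
| 0 | 81% | 5.0% | 81% |
| 0.5 | 80% | 4.6% | 81% |
| 1 | 77% | 3.8% | 81% |
| 1.5 | 73% | 2.7% | 81% |
| 2 | 66% | 1.7% | 81% |

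The period-adjusted test compares within-subject period differences between sequences on 24 df. Its exact power is 80.8%, against 81.0% for the paired t-test when P = 0: a cost of 0.1 to 0.2 points.

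**4. Unequal sequences.** At 15:11 the bias is P × 4/26 = 0.154 × P in absolute size: 0.08 at P = 0.5, 0.15 at P = 1 and 0.31 at P = 2. Its sign depends on the direction of P and on which sequence is larger. If it works against metformin, paired-t power is about 69% at P = 1, against 80% for the adjusted test; if it works in favour, power rises to about 84% for the wrong reason. Type I error at 15:11 is 4.5% at P = 1 and 4.0% at P = 1.5, so it is not inflated.

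**The case against.** The strongest reply is that P may be close to zero. The endpoint is a change within a session, so a shift in FMD level between visits (drift in scanning, familiarisation with the procedure) cancels; only a shift in the response to IR counts. Section 3 also fixes time of day, room temperature, fasting, caffeine, exercise and menstrual timing, and has the same sonographer measure before and after IR. P = 2 would be 77% of the whole stated IR effect (2 / 2.6). For P up to 1 the loss is at most about 3.5 points. All of this stands and limits the size of the point. It does not justify omitting period, because adjusting costs almost nothing if P is zero.

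A second reply is that 15:11 is speculative. That is also fair: it takes at least two withdrawals with replacements landing in the other sequence, and the protocol gives no dropout rate. Section 7.5 does not say that replacements ignore the vacated sequence; it is silent.

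A reader might infer that the primary estimate is biased as planned, or that replacement itself costs power. The protocol supports neither. At 13:13 there is no bias at any P, and replacement keeps n at 26. Nor does the protocol show an inflated false-positive rate: at 13:13 the test is conservative, and at 15:11 it stays below 5%. In the simulations type I error reaches only 5.7% at 16:10 and is clearly inflated only at an extreme 18:8 (8.4% at P = 1).

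**Conclusion.** The point holds in a limited form. The protocol fixes a primary test that does not use the order it randomises. At the planned 13:13 split the result is a valid but conservative test whose power falls from about 81% to 80%, 77%, 73% and 66% at P = 0.5, 1, 1.5 and 2, where a period-adjusted test keeps about 81%. Bias arises only if there is a period effect and the sequences also become unequal, which section 7.5 leaves open; at 15:11 it is 0.154 × P.

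These figures rest on the protocol's SD of 2.85 and effect of 1.65, a two-sided 5% test, and assumed values of P and of the split. The sample size statement in section 4.4 is not undermined. The primary analysis remains usable; it is avoidably weaker than the design allows.

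**What to change.** - **Section 9.2:** replace the paired t-test for the metformin effect by a period-adjusted cross-over analysis of the IR-induced change. Either compare within-subject period differences between the two sequences, or fit an equivalent model with treatment and period as fixed effects and subject as a random effect. Section 9.3 should then not read as excluding it.
- **Section 7.5:** add one sentence saying that each replacement takes the sequence of the withdrawn subject.

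The cost is one residual degree of freedom (24 instead of 25), or 0.1 to 0.2 points of power at 13:13 if there is no period effect. No visits, measurements or subjects are added.
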